### Confidentiality {27}

All the study-related information will be stored securely at the study site. All participant information will be stored in locked file cabinets in areas with limited access. All questionnaire forms will be identified only by a coded ID (identification) number in order to maintain participant confidentiality. All records containing names or other personal identifiers will be stored separately from study records identified by a code number. All databases will be secured with password-protected access systems. Lists that link participant ID numbers to other identifying information will be stored in a separate, locked file in an area with limited access.

Participants’ study information will not be released outside the study without their written permission.

### Plans for collection, laboratory evaluation and storage of biological specimens for genetic or molecular analysis in this trial/future use {33}

Not applicable. This trial does not use biological specimens.

## Statistical methods

### Statistical methods for primary and secondary outcomes {20a}

#### Statistical analysis of the subjective variables

All analyses will be conducted using SPSS24.0 software. Firstly, ANOVAs and chi-square tests will be conducted to determine whether significant differences exist between the different intervention groups for the variables collected (PROMIS and PANAS scales) in the first assessment phase (Time 1) and for the level of immersion when viewing the film clip during the negative mood induction. If differences between groups are found in any of these variables, the variables with statistically significant differences will be included as covariate variables in the following ANOVAs. Secondly, to assess the impact of personal relevance of the images in emotional recovery, a repeated-measures ANOVA and post hoc Bonferroni tests will be performed in a mixed design with type of image (low, medium and high personal relevance groups) and group (young and older) as between-subjects variables and time (pre-test—Time 1—, post-negative emotional induction—Time 2—and post-positive emotional induction—Time 3) as within-subject variables. Finally, to assess the sense of reliving for the three groups of images, a repeated-measures ANOVA and post hoc Bonferroni tests will be performed in a mixed design with type of image (low, medium and high personal relevance groups) and group (young and older) as between-subjects variables and (average score of concentration level recalling the events and average score of the degree of reliving the positive emotions of the remembered events) as within-subject variables.

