**Fig. 1 Fig1:**
[figure not shown]
Randomization phase

We will thus have three types of images varying in their level of personal relevance for each participant. The first type of images is pictures taken for the standardized IAPS. There will be a total of 40 pictures selected by the research team according to their level of positive valence (emotional valence values between 7.03 and 8.34). The participants will be asked to choose the 6 photos that best enable them to generate a specific positive autobiographical memory.

The second type of images used will be photos of locations and places that are significant for the participant, which will be selected following a prior interview in which the participant will be asked to name places that evoke specific positive autobiographical memories. These images will be taken from the Internet. We will select various images of each location, giving participants the opportunity to choose the one which best fits their memory.

The third type of images will be autobiographical photographs selected by participants from their own collection. Participants will be asked to previously select six photos, for which they can recall the exact moment they were taken and which are related to events that have made them feel happy during their lives. These six events will be those they are asked to recall in the experimental task.

For each of the memories retrieved in the three conditions, the following factors will be assessed: (1) the degree of nostalgia generated by the memory; (2) the intensity of the positive emotion evoked by the memory; (3) whether the participant was a spectator in the event (“as if I were watching a film”) or an actor (“as if I were seeing it with my own eyes or recording it”); (4) the significance of the event in the person’s life; (5) personal growth since the event occurred; (6) belief that the event has led them to better understand themselves and what life means; and (7) belief that they have learnt more about what life means as a result of the event.

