**Fig. 2 Fig2:**
[figure not shown]
Experimental phase

At the start of the experiment, all the participants will be asked to complete the PANAS mood state scale [88]. This scale will be completed on three occasions: at the start of the task, following the negative mood induction (viewing the film clip) and after the autobiographical memory task (presentation of images according to the assigned experimental condition).

After completing the PANAS [88], the negative mood induction phase will begin. The participants will watch a 7-min section of the film “Dead Man Walking” (Polygram Filmed Entertainment, Havoc, Working Title Films), which shows the execution of a prisoner sentenced to death. Before seeing the film clip, the participants will be encouraged to experience the feelings generated by the clip as intensely as possible. After viewing the film clip, they will be asked to answer the control questions related to their level of concentration while watching the clip, and the degree to which they surrendered to the feelings it generated. They will then be asked to complete the PANAS [88] again in order to assess the effectiveness of the negative mood induction procedure.

Following the negative mood induction phase, the emotional recovery phase will be initiated, in which the participants will look at a total of six pictures previously selected according to their experimental condition in order to generate specific positive autobiographical memories. Each image will be presented for 1 min, and during this time, the participants will be asked to concentrate as hard as they can on the memory that each picture evokes with the aim of reliving the positive emotions they felt at that moment as intensely as possible. After each picture, the participants will answer a series of control questions related to their level of concentration while looking at the pictures and to what extent they were able to relive the emotions they felt at the moment related to the images. At the end of this phase, participants will once more complete the PANAS [88] in order to assess the effectiveness of the emotional recovery.

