### Participant timeline {13}

Participant recruitment is expected to begin in October 2020 and continue for 2 months. Nevertheless, if the minimum number of participants in each experimental group is not reached in early December, the recruitment period will be extended until the required minimum is reached. In this phase, those who agree to participate will complete the screening questionnaires.

The pre-experimental and experimental phases will take place 7–21 days after randomization. Both phases will take place on the same day. In the pre-experimental phase, participants will select the images to be displayed in the experimental task according to the group to which they are assigned (low, medium or high personal relevance). Finally, in the experimental phase, they will complete the mood questionnaires and the experimental task.

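### Film immersion is rated after randomisation and after arm-specific picture selection, yet a significant arm difference makes it a covariate; this can bias the arm comparison

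*Protocol article*

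**What the plan says.** *Statistical analysis of the subjective variables* begins with tests of the intervention groups on the PROMIS and PANAS scores at Time 1 and "for the level of immersion when viewing the film clip during the negative mood induction". It then states that "the variables with statistically significant differences will be included as covariate variables in the following ANOVAs". Those ANOVAs include the main one: image type and age group between subjects, and three PANAS times within subjects.

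*Participant timeline {13}* fixes the order of events. "The pre-experimental and experimental phases will take place 7–21 days after randomization", and "Both phases will take place on the same day". In the first of these phases, "participants will select the images to be displayed in the experimental task according to the group to which they are assigned"; the schedule table allows 25 minutes for it. *Experimental phase* then has the first PANAS, the film and the immersion items: "After viewing the film clip, they will be asked to answer the control questions related to their level of concentration while watching the clip". The six pictures are viewed only after that.

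*Control questions following negative mood induction* defines immersion as two self-ratings from 0 to 9: concentration, and surrender to the feelings the clip generated. *Who will be blinded {17a}* says that neither participants nor the psychologists running the session can be blinded.

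**The concern.** A covariate in a randomised comparison should be a variable that the allocation cannot have changed. Film immersion does not meet that condition. Before the film, one arm has picked stock pictures, one has chosen images of places tied to good memories, and one has worked with its own happy photographs. Participants know which arm they are in. Either fact could make them surrender more, or less, to a distressing clip.

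Immersion and later mood ratings plausibly share causes that are not measured, such as emotional reactivity. If the arm moves immersion, holding immersion fixed compares people in different arms who differ on those causes. An effect of personal relevance on recovery could then be created or hidden. The significance trigger makes this worse, because it admits the covariate most often when the arm has affected it.

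**Working it through.** **Order of events.** Randomisation; 7 to 21 days later, arm-specific picture selection; the same day, PANAS Time 1; film; immersion items and PANAS Time 2; picture viewing; PANAS Time 3. So immersion follows allocation and picture selection but precedes picture viewing. PANAS Time 1 also follows picture selection.

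**Inputs.** From the protocol: 40 per arm in each of two age groups, so 2 × 40 = 80 per arm and 3 × 80 = 240 in all; tests at 5%. Assumed, because the documents give neither: an immersion shift δ of 0.3 or 0.5 SD in one arm, and a within-arm correlation r of .3 or .5 between immersion and mood, arising only from a shared unmeasured cause. There is no true arm effect on mood. The protocol states no figure to reproduce here.

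**How often the rule adds immersion.** For one immersion score, the noncentrality of the three-arm test is 80 × the sum of squared deviations of the arm means.
- One arm shifted: 80 × (2/3)δ². δ = 0.3 gives 4.8, triggered in about 48% of trials; δ = 0.5 gives 13.3, about 91%.
- Shift graded evenly across the arms, with δ between the extremes: 80 × δ²/2. This gives 3.6 and 10.0, or about 37% and 81%.
- No arm effect: 5% per item, or 1 − 0.95² = 9.75% for at least one of two items if tested separately and independent.

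**Bias when immersion is added.** In SD units the adjusted arm difference is off by about δ × r, with sign opposite to the immersion shift. For a difference between two PANAS times, r is replaced by the difference between the two correlations.

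Time 3 score alone (simulation, 4,000 runs, one arm shifted):

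| δ | r | δ × r | Simulated bias, SD | Type I error under the rule |
|---|---|---|---|---|
| 0.3 | .3 | 0.09 | 0.09 | 6.6% |
| 0.3 | .5 | 0.15 | 0.15 | 11.0% |
| 0.5 | .3 | 0.15 | 0.15 | 15.0% |
| 0.5 | .5 | 0.25 | 0.25 | 39.5% |

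Without immersion in the model, type I error is about 5%. With no arm effect on immersion, adjusted bias is about 0 and type I error about 5%.

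**The planned arm-by-time test, same settings.**
- Shared cause is a stable trait with equal influence at all three times: the correlations are equal and cancel. Type I error was 4.5% to 5.0%, and bias in Time 3 minus Time 2 was 0.00 SD.
- Shared cause acts only from the film onward: the correlation is 0 at Time 1 and r at Times 2 and 3. Time 3 minus Time 2 stays unbiased, since r − r = 0. Time 3 minus Time 1 is off by δ × r, again 0.09 to 0.25 SD. One run gave type I errors of about 5%, 9%, 10% and 23% across the four settings.
- A further run, with the cause starting at the film or fading afterwards, gave about 5% to 16%. If it fades, Time 3 minus Time 2 is biased as well, because the two correlations differ.

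**The case against.** The strongest reply concerns the question being asked. The trial studies recovery after a negative mood induction, and immersion gauges how strongly the induction took. Suppose immersion itself drives mood at Times 2 and 3, with no shared unmeasured cause. An arm that was less immersed was then induced less, and the unadjusted comparison credits its pictures with that. Under this assumption the unadjusted Time 3 difference departs from the effect at equal induction by 0.09 to 0.25 SD, and the arm-by-time test rejects in 7% to 16% of trials. Adjusted bias is about 0.

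This shows that an immersion-adjusted result can answer a legitimate second question. It does not rescue the rule. That answer requires no unmeasured common cause of immersion and mood, which the protocol does not state, and a significance test on the arms is no guide to whether it holds. The unadjusted result remains a valid estimate of the total effect of assignment.

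It is also fair that the trial calls itself exploratory, that the bias is conditional, and that its direction is unknown.

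Two stronger readings are tempting. A reader might infer from the Time 3 table that the planned analysis has a false-positive rate of up to 40%. The documents do not support this: the main ANOVA uses three times, and its arm-by-time test is inflated much less or not at all. A reader might also infer that viewing the pictures contaminates immersion. It cannot, because the immersion items come first. The possible routes are picture selection and knowledge of the arm.

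**Conclusion.** The concern holds as a defect in a stated rule. The protocol lets a self-rated, unblinded, post-randomisation variable into the main arm comparison, and does so when the arms differ on it. Bias requires both that the arm affects immersion and that immersion shares unmeasured causes with mood after the film. The documents establish that the first is possible, not that it happens. Every size quoted depends on the assumed shifts and correlations.

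The arm-by-time figures are the relevant ones for the planned test, and their upper values need the larger shift and the larger correlation together. The rule should be changed, but nothing here shows that the results will be wrong. Time 1 PANAS, listed in the same sentence, shares the timing problem.

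**What to change.** In *Statistical analysis of the subjective variables*:

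- Remove film immersion from the variables that can become covariates in the main ANOVAs, and report it by arm as a check on the induction.
- Restrict covariates to variables recorded before randomisation and chosen in advance, for example the screening PROMIS scores, with no significance trigger. Dropping the trigger alone would not be enough, since immersion could still be chosen as a covariate.
- Keep Time 1 PANAS as the first level of the outcome, and do not also add it as a triggered covariate.
- If the sponsor wants the effect at equal induction, show an immersion-adjusted result as a labelled sensitivity analysis, stating the assumption of no unmeasured common cause.

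This is a short edit and needs no new data. The cost is a small loss of precision if immersion predicts mood and is unaffected by arm. The main result then estimates the total effect of assignment, including any effect of picture selection on the induction, and the report should say so. In the simulations, leaving immersion out kept the estimate within 0.01 SD of the true value of 0 and type I error at 4.4% to 5.8%.

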##### Patient-Reported Outcomes Measurement Information System-D (PROMIS®-Depression 4ª, short form) [85]

This version includes four items to measure a participant’s negative affect in the past 7 days, with five response options ranging from 1 = never, to 5 = always, where the higher the score, the greater is the negative affect. The test forms part of PROMIS-29, and total scores range between 4 and 20, where the highest scores correspond to more serious depressive symptoms [89]. The cut off is set at 11 points (http://www.helathmeasures.net). Indices of reliability for this version are excellent (*α* = .96).

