#### Control questions

##### Control questions following negative mood induction

To measure the participant’s level of immersion in the film clip used for negative mood induction, the following questions are used: (1) On a scale from 0 to 9, indicate your level of concentration while watching the film clip (0 = no concentration; 9 = total concentration), and (2) on a scale from 0 to 9, indicate to what degree you surrendered to the feelings generated by the film clip (0 = I did not surrender at all to the feelings in the film clip; 9 = I surrendered totally to the feelings in the film clip).

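### If covariates enter the SPSS repeated-measures ANOVA as scored, the omnibus time effect is tested at covariate = 0; the plan should say that they are centred

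*Protocol article*

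**What the plan says.** The relevant text is in the protocol article, under Statistical analysis of the subjective variables.

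- **Software:** "All analyses will be conducted using SPSS24.0 software".
- **Candidate covariates:** the groups are first compared on their PROMIS scores and the first PANAS. The same check is made "for the level of immersion when viewing the film clip during the negative mood induction".
- **Entry rule:** where groups differ, "the variables with statistically significant differences will be included as covariate variables in the following ANOVAs". Nothing is said about raw or centred entry.
- **Model:** a mixed ANOVA with image type and age group between subjects, time (three levels) within subjects, and post hoc Bonferroni tests. Its stated purpose is the effect of image relevance on emotional recovery.

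The outcomes section gives the scales. For PROMIS-Depression, "total scores range between 4 and 20"; PROMIS-Anxiety has the same range. Each PANAS subscale has ten items scored 1 to 5, so it runs from 10 to 50. Immersion is asked as "On a scale from 0 to 9, indicate your level of concentration while watching the film clip", with a second item on the same 0 to 9 scale.

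Under Experimental phase, after the film participants "complete the PANAS [88] again in order to assess the effectiveness of the negative mood induction procedure"; the PANAS after the pictures serves the same purpose for recovery.

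**The concern.** In a repeated-measures general linear model, the time main effect is the test of the intercept of the within-subject contrasts. Once a covariate is in the model, that intercept is the mean change at covariate = 0. SPSS GLM does not centre covariates itself. Entered as scored, they shift the null hypothesis from no change in the people studied to no change in a person with an impossible or extreme score.

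Time 1 PANAS is the sharpest case, because it is also the first level of the time factor. Its slope on change from Time 1 is therefore non-zero by construction.

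At stake is how one line of output is read. A reader who takes the time F as evidence that the film lowered mood, or that mood recovered, could be misled either way, and that line could disagree with the pairwise comparisons printed beside it.

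**Working it through.** The plan states no figure on this point, so there is none to reproduce. N = 240 (six cells of 40), three times and alpha .05 come from the protocol. Every mean, SD and correlation below is an assumption, because the protocol gives none for these scales.

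**1. Loss of precision.** For a covariate with mean m and SD s, the standard error of the intercept at 0 is larger than at the mean by √(1 + m²/s²):

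- PROMIS, m = 6.5, s = 2: √(1 + 10.56) = 3.40
- Immersion, m = 7, s = 1.5: √(1 + 21.78) = 4.77
- PANAS, m = 32, s = 7: √(1 + 20.90) = 4.68

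**2. Shift of the null.** Let the covariate correlate r with the Time 1–2 change. With no mean change, the contrast tested at 0 has approximately

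t = r(m/s)√N / √[(1 − r²)(1 + m²/s²)].

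For PROMIS (m/s = 3.25, √240 = 15.49) this gives 1.49, 3.02 and 4.66 at r = .1, .2 and .3. Because m/s is large, t is close to r√N: the raw time F largely repeats the covariate × time test.

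Simulation for PROMIS (mean 6.5, SD 2, correlation between times .6; ranges are across separate runs with slightly different handling of the scale limits):

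| r | False rejection, raw | Power for a 0.5-SD rise in negative affect, raw |
|---|---|---|
| 0 | 5% | 58–63% |
| .1 | 25–34% | 11–14% |
| .2 | 78–90% | 7–13% |
| .3 | 99–100% | 47–69% |

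Centred, false rejection was 3–6% and power 100% throughout.

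Power falls and then rises because the tested intercept crosses zero. The SD of change is √(2 × .4) = .894, so 0.5 SD is .5/.894 = .559 in units of change, and the crossing is at r = .559/3.25 = .17. With r negative the shift adds to the effect: raw power was 89–94% at r = −.1 and 100% at −.2 and −.3. For immersion (mean 7, SD 1.5), raw power at r = 0, .1, .2 and .3 was 39%, 5%, 19% and 79%, against 100% centred.

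Milder assumptions give milder results. With PROMIS mean 6, SD 2 and a slope of 0.15 per point on the Time 2 score, raw false rejection was 9% against 4% centred. With slopes from −0.15 to +0.15, raw power for a true 5-point dip was 90–100%.

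**3. Time 1 PANAS as covariate.** With equal variances and correlation ρ between times, the slope of change on Time 1 is ρ − 1. With no true change, the change tested at 0 is d = (1 − ρ)m. For m = 32, SD 7, ρ = .6:

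- d = .4 × 32 = 12.8 points, where the truth is 0.
- Effect mean square per participant: (2d²/3)/2 = 54.6.
- Residual variances at Times 1, 2 and 3, given Time 1: 0, 31.36 and 31.36; covariance of Times 2 and 3: 11.76. Error mean square: [62.72 − (62.72 + 23.52)/3]/2 = 16.99.
- F ≈ 240 × 54.6 / (21.90 × 16.99) = 35.2.

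The simulated median F was 35.4, with rejection 100% raw against 9% centred. Across ρ from .4 to .9, and mean/SD of 32/7 or 15/5, rejection was 94–100% raw and 5–10% centred. The centred figure exceeds 5% because the model treats the sample mean of Time 1 as fixed: it counts a change variance of (1 − ρ²)s² = .64s², where the full variance is 2(1 − ρ)s² = .80s².

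**4. What is not affected.** The F values for image type × time and image type × age × time were the same raw and centred, to rounding error. The Bonferroni Time 1–2 comparison, evaluated at the covariate mean, kept 100% power at 0.5 SD and rejected in 1–4% of runs under no change.

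**5. How often it could arise.** With six candidates (two PROMIS, two PANAS, two immersion), independent and with no true group difference, the chance that at least one enters is 1 − .95⁶ = 26.5%. Positive correlation between them would lower this.

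**The case against.** The strongest reply is that the article fixes no covariate coding. Raw entry is inferred from silence, and centring is a detail usually left to the analysis plan. That stands, so the point is conditional on raw entry. What keeps it alive is that the article itself fixes the software, model, time factor and covariate rule, and these followed literally give the misdirected test.

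Second, the ANOVA's stated purpose is the effect of image type on recovery, which is unaffected. That stands in full. A reader might infer that the comparison of the three image types is biased; it is not.

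Third, a reader might infer that the omnibus time F is the plan's test of induction and recovery. The Experimental phase section names no test, and a three-level omnibus F can neither locate nor sign a change. The planned Bonferroni comparisons can, and SPSS evaluates them at the covariate mean. This also stands.

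Fourth, covariates enter only after a significant group difference, and 0 is an attainable score for immersion and for PANAS affective balance. Both are correct and limit the reach of the point.

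Finally, the simulated sizes rest on assumed inputs, and the power figures depend on the sign of r. They show what can happen and do not forecast this trial's results.

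**Conclusion.** The concern holds in a limited form. If a covariate is admitted and entered as scored, the omnibus time main effect answers the wrong question. Under the assumptions shown, false rejection with PROMIS ranges from about nominal (5% at r = 0) to near certain (99–100% at r = .3), and power for a 0.5-SD induction from 7% to 100% depending on the size and sign of r. With Time 1 PANAS as covariate the result hardly depends on the inputs: 94–100% false rejection over the range tried.

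The arm comparisons, the age interaction and the pairwise time contrasts are sound either way. This is a minor clarification worth making because it is free. It is separate from whether covariates should be chosen by significance tests at all.

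**What to change.** In Statistical analysis of the subjective variables, after the covariate rule, add: *each covariate is centred at its overall sample mean before entry*. Alternatively, take the time main effect from the ANOVA without covariates and keep the covariates for the image-type and image-type × time tests. If Time 1 PANAS is admitted, the second option also avoids the small excess over 5% that remains after centring.

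In either case, state that induction (Time 1–2) and recovery (Time 2–3) are judged from the pairwise contrasts, evaluated at the covariate mean where covariates are in the model.

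The cost is one or two sentences and one compute step per covariate. No new data are needed, and the arm comparisons do not change.

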### Interventions

#### Explanation for the choice of comparators {6b}

The conditions of medium and high personal relevant images will be compared with IAPS images (low personal relevant condition). IAPS [41] is traditionally considered a valid system for affectively eliciting stimuli that can be used as a representative tool, for example, in mood and emotion induction studies. For this reason, its selection as comparator is justified.

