### Sample size {14}

This study requires a sample of 120 participants aged 65 or older (divided into three groups of 40) without cognitive impairment or major depressive disorder, and 120 young adults aged between 18 and 35 (divided into three groups of 40) with no major depressive disorder.

To calculate the sample size, we used GPower version 3.1., considering the following parameters: a 95% confidence interval (*p* < .05), an estimated power of 95%, a predicted medium effect size of 0.06 (partial eta squared; Cohen [94]), 6 repeated measures (6 pictures), an expected correlation between of .80 and 6 experimental groups (3 types of pictures × 2 age groups).

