We will calculate the mean SCL and HR values recorded for 4 min before the start of the negative mood induction procedure. These will be compared with the maximum scores obtained in the experimental phases (negative mood induction—viewing film clip—and emotional recovery using images). Independently for SCL and HR variables, repeated-measures ANOVA and post hoc Bonferroni tests will be performed in a mixed design with group (low, medium and high personal relevance groups) as between-subjects variable and time (pre-test—Time 1; post-negative emotional induction—Time 2; and postpositive emotional induction—Time 3) as within-subject variables.

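### Post hoc Bonferroni on the three image types is valid but needlessly conservative; a closed or step-down procedure keeps the 5% familywise cap and gives more power per pair

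*Protocol article*

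**What the plan says.** In the section on statistical analysis of the subjective variables, the mood analysis is a mixed ANOVA: image type (three levels) and age group (two levels) between subjects, and time (three levels) within subjects. The pairwise step is fixed there: "a repeated-measures ANOVA and post hoc Bonferroni tests will be performed in a mixed design with type of image". The reliving analysis in the same section uses the same device. The data analysis part of the HRV and EDA section repeats it without the age factor: "repeated-measures ANOVA and post hoc Bonferroni tests will be performed in a mixed design with group (low, medium and high personal relevance groups". The software is named ("All analyses will be conducted using SPSS24.0 software"). No list of pairs, adjusted level, planned contrast or stepwise procedure is given.

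The section on the choice of comparators {6b} says "The conditions of medium and high personal relevant images will be compared with IAPS images (low personal relevant condition". Objectives {7} and Trial design {8} speak more broadly of comparing all three image types, and Trial design calls the study exploratory.

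Sample size {14} gives 40 per image arm in each age group, so 80 per arm pooled over age. It assumes "an estimated power of 95%, a predicted medium effect size of 0.06" in partial eta squared, and "6 repeated measures (6 pictures), an expected correlation between of .80 and 6 experimental groups". It gives no pairwise effect and no standard deviation.

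**The concern.** Whether more personal pictures aid recovery better than standard ones will be read from the pairwise tests. Bonferroni on a three-level factor splits .05 over three pairs. With exactly three arms that is more protection than the 5% cap requires. If any two of the three pairwise nulls are true, the third is true as well, so once the global null is rejected at most one pairwise null can still hold. Testing each pair at .05 after that step keeps familywise error at 5%.

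What is at stake is power, mainly for the middle arm. If the effect is graded, medium vs IAPS is the weaker of the two comparator contrasts and the one most easily missed. A report could then conclude that own photographs work and pictures of places do not, when the truth is a gradient.

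**Working it through.** **The plan's own figure.** Take f² = .06/.94 = 0.0638, so f = 0.2526. The between-factors repeated-measures formula gives λ = f²·N·m/(1 + (m − 1)ρ) = 0.0638 × 240 × 6/(1 + 5 × .80) = 18.4. With 5 and 234 df, power at N = 240 is .926, and 264 participants are needed for 95%. The stated 240 is therefore not reproduced by this formula (ρ = .70 would give 239). That is a separate matter, and nothing below depends on it.

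**Inputs.** From Sample size {14}: α = .05, f = 0.2526, 40 or 80 per arm. Assumed: two-sided tests; three pairs at .05/3 = .0167; the .06 read as an image-type effect on one recovery score with unit SD; and the patterns of means.

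**Pairwise effects implied by f.**
- Evenly spaced means (−a, 0, a): a·√(2/3) = f, so a = 0.309. Hence d = 0.309 for medium vs IAPS and 0.619 for high vs IAPS.
- One arm apart from the other two by δ: δ·√2/3 = f, so δ = 3f/√2 = 0.536.

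**Hand check, medium vs IAPS, 80 per arm, even spacing.** The noncentrality is 0.309 × √(80/2) = 1.96. At .0167 (normal quantile 2.394), power is about Φ(1.96 − 2.394) = Φ(−0.44) = .33. At .05 (quantile 1.960), it is about Φ(0) = .50. The simulation gives .326 and .496 for these two unconditional tests.

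**Simulation** (400,000 runs, pooled variance). The closed procedure is the 2-df F test at .05, then each pair at .05. Shaffer's step-down tests the smallest p at .0167 and, if that is rejected, the other two at .05.

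| Pattern, n per arm | Contrast | Bonferroni | Closed | Shaffer |
|---|---|---|---|---|
| Even, 80 | medium vs IAPS | .326 | .493 | .490 |
| Even, 80 | high vs IAPS | .932 | .943 | .938 |
| High = medium, 80 | each vs IAPS | .836 | .905 | .89 |
| High only, 80 | high vs IAPS | .836 | .905 | .893 |
| Even, 40 | medium vs IAPS | .152 | .265 | .254 |
| Even, 40 | high vs IAPS | .633 | .674 | .653 |
| High = medium, 40 | each vs IAPS | .49 | .595 | .566 |
| High only, 40 | high vs IAPS | .490 | .594 | .566 |

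**Error rates.** Under the global null, familywise error is .043 with Bonferroni and .050 with the closed procedure. Shaffer's first step is the Bonferroni step, so its rate there is also .043. When only the high arm differs, and by a large amount, the rate of falsely claiming medium vs IAPS is .017 with Bonferroni and .050 with either alternative.

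**What the overall test costs.** At the planned effect, a pair that Bonferroni would declare but the F test blocks occurs in at most 0.5% of runs (largest case .633 vs .628). Shaffer's procedure cannot lose such a pair.

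**How large the gain can be.** For one contrast, the largest power difference between testing at .05 and at .0167 is 17.2 points. The 16.7 points for medium vs IAPS (.493 − .326) is therefore close to the ceiling.

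**The case against.** The strongest reply is that nothing here is wrong. Bonferroni controls familywise error, the study is exploratory, and choosing between valid methods is partly taste. The first part stands: this is not an error. But the article itself fixes the method, and the alternative gives more power for every true difference in every pattern tested, so it is more than taste.

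A reader might infer that all-pairs testing contradicts the comparator section, which names only the two contrasts with IAPS. The documents do not support this. That section justifies IAPS as comparator and does not list the hypotheses; Objectives and Trial design put high vs medium within the aim. For the same reason I do not propose dropping that pair. Bonferroni on the two IAPS contrasts alone would give slightly more for high vs IAPS at 40 per arm with even spacing (.690 against .67 closed), but less for medium vs IAPS (.192 against .265), and it would leave out a comparison the protocol wants.

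A reader might also infer a general loss of 17 points, or a gain free of any error cost. Neither holds. Seventeen is the best case, and high vs IAPS gains about 1 to 10 points depending on pattern and arm size. Only the 5% cap is unchanged; the error rate on a single true-null pair roughly triples, from 1.7% to 5%.

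It is also fair that the harm is reduced, not removed. With 80 per arm and even spacing, the closed procedure still misses medium vs IAPS in 51% of runs. The outcome of high significant and medium not falls from .932 − .322 = 61% to .943 − .492 = 45%.

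Last, the planned 3 × 2 × 3 ANOVA has no ready 2-df test of recovery. The image-type main effect averages three times, two of them before the pictures are shown, and image type × time has (3 − 1)(3 − 1) = 4 df. This stands, and the fix has to supply the contrast.

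**Conclusion.** The concern holds as a point of efficiency. For one score compared across three arms, post hoc Bonferroni gives up power that a closed or Shaffer procedure recovers within the same 5% familywise cap. At the planned effect with 80 per arm, the gain is about 17 points for medium vs IAPS under even spacing, about 7 points for each IAPS contrast when high = medium, and about 1 point for high vs IAPS under even spacing.

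The sizes rest on assumptions: the patterns of means, unit SD, two-sided tests, and reading the .06 as an effect on a single recovery score. All three pairs at .0167 is likewise inferred from the number of levels and is not printed in the protocol. The guarantee is per outcome and for one three-arm family. It does not cover pairs within both age groups taken together, several time points, or several outcomes.

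**What to change.** In the subjective-variables section and in the HRV and EDA section, replace the post hoc Bonferroni tests for image type as follows.

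- For each outcome, define one recovery contrast, for example the change from Time 2 to Time 3, pooled over age. Test image type on it with 2 df at .05.
- If that test is significant, test high vs IAPS, medium vs IAPS and high vs medium, each at .05.
- Alternatively, omit the overall test and use Shaffer's step-down: smallest p at .0167, then the other two at .05. It never rejects less than Bonferroni and gives nearly the same gain.
- State that the 5% guarantee is per outcome for one three-arm family and does not extend across age groups, time points or outcomes.

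No further data or participants are needed; the work is to define the contrast and reword the two sections. There are three small downsides. Unadjusted intervals for the pairs are not simultaneous. With the overall test, no pair can be claimed if that test fails. The error rate on a single true-null pair rises from about 1.7% to the nominal 5%.
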